## Abstract

**Background::**

Essential hypertension is a multifactorial disease, which is affected by genetic and environmental factors, and can cause diseases such as cerebrovascular disease, heart failure, coronary heart disease, and chronic renal failure. High salt intake is a risk factor for hypertension, stroke, and cardiovascular disease. Blood pressure variability (BPV) is a reliable independent predictor of cardiovascular events and death. At present, there are few studies about the correlation among high salt intake, BPV, and target organ damage (TOD) in patients with hypertension.

**Objective::**

The purpose of this study is to compare 24-hour urine sodium excretion, BPV, carotid intima–media thickness, left ventricular mass index, and serum creatinine or endogenous creatinine clearance rate. To clarify the relationship between high salt load and BPV and TOD in patients with hypertension.

This study is a cross-sectional study. It will recruit 600 patients with essential hypertension in the outpatient and inpatient department of cardiovascular medicine of Chengdu Fifth People's Hospital. Researchers will obtain blood and urine samples with the patient's informed consent. In addition, we will measure patient's blood pressure and target organ-related information.

**Trial registry::**

The study protocol was approved by the Chengdu Fifth People's Hospital. Written informed consent will be obtained from all the participants. The trial was registered in the Chinese Clinical trial registry, ChiCTR2000029243. This trial will provide for the correlation among high salt intake, BPV, and TOD in patients with essential hypertension.

## Introduction

1

Essential hypertension is a common circulatory system disease, which is affected by both genetic and environmental factors,^[1]^ and accounts for more than 40% of the cardiovascular disease total burden.^[2]^ High salt intake can not only increase blood pressure, but also reduce the efficacy of antihypertensive drugs. And 24-hour urine sodium test is the best way to measure an individual's daily sodium intake.^[3]^ Blood pressure variability (BPV) is a basic characteristic of blood pressure and can reflect the magnitude of blood pressure fluctuations over a period of time. Recent research shows that BPV can better reflect cardiovascular activity than blood pressure levels and is more closely related to target organ damage (TOD) in hypertension.^[4–6]^ Failure to detect and treat essential hypertension early can damage important organs such as the heart, brain, and kidneys, causing diseases such as left ventricular hypertrophy, atherosclerosis, and renal failure.^[7,8]^ Left ventricular hypertrophy (LVH) is an independent cardiovascular risk factor in patients with essential hypertension.^[9,10]^ Intima–media thickness (IMT) is a marker that can be used to assess the severity of atherosclerosis.^[11]^ Serum creatinine, endogenous creatinine clearance rate (Ccr) and 24-hour urine microalbumin (MA) were commonly used indicators of renal function. However, the relationship among high salt load, BPV, and TOD in patients with hypertension is unclear. This study recruited patients with essential hypertension in the Department of Cardiovascular Medicine of Chengdu Fifth People's Hospital. Collect basic patient information, blood pressure measurements, blood specimens, 24-hour urine specimens, and other clinical examination results. Carotid IMT, left ventricular mass index (LVMI), serum creatinine or Ccr, 24-hour urine MA, and other indicators were used to evaluate TOD. To clarify the relationship among high salt intake, BPV, and TOD. To lay a good foundation for early detection of TOD in essential hypertension and related measures.

## Materials and methods

2

### Aim of the study

2.1

The objective of this study is to investigate the relationship among high salt intake, BPV, and TOD in patients with hypertension. Through laboratory inspection, echocardiography, and ambulatory blood pressure monitoring, we could identify risk factors and take steps to reduce the risk of damage to the patient's target organs.

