#### Ambulatory blood pressure monitoring

2.5.3

All subjects used a fully automatic noninvasive cuff blood pressure monitor (fixed model) for blood pressure monitoring. The cuff is fixed to the subject's left upper arm and can be used for daily work and activities, but strenuous exercise should be avoided. Monitoring time: measured every 30 minutes during the day (8:00–22:00), every night at 22:01 to 7:59 the following day, every hour. The daily effective blood pressure reading is greater than 85% of the set number, and the effective value needs to be greater than 48 times. Effective blood pressure readings: SBP 70–260 mm Hg (1 mm Hg = 0.133 kPa), DBP 40 ∼ 150 mm Hg, pulse pressure 20 ∼ 120 mm Hg. Monitoring indicators: 24-hour mean SBP (24-h SBP), 24-hour mean DBP (24-h DBP), day-time mean SBP, night-time mean SBP, day-time average DBP, and night-time mean DBP. The blood pressure standard deviation (SD) and its coefficient of variation (CV) at each time period were used as indicators of BPV at that time period. (CV-SBP, coefficient of variation of systolic blood pressure) CV is the ratio of the SD to the mean. Expressed by the formula: CV = σ/μ. Monitoring normal reference value: 24 hour mean blood pressure <130/80 mm Hg, daytime blood pressure <135/85 mm Hg, nocturnal blood pressure <120/70 mm Hg. Blood pressure circadian rhythm = (average blood pressure during the day − average blood pressure during the night) / average blood pressure during the day; >10% is normal blood pressure circadian rhythm (dipper type hypertension), otherwise it is nondipper type hypertension, <0 is the anti-dipper type hypertension; CV-SBP is grouped with a cutoff of 12%.

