#### Grouping criteria

2.5.6

Twenty-four-hour urinary sodium was used to estimate sodium salt intake. Based on the quartiles of the 24-hour urine sodium, the enrolled population was divided into low sodium group, low-to-medium sodium group, medium-to-high sodium group, and high sodium group.

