### Statistical methods

2.7

We will use SPSS 17.0 software for statistical analysis in this study. Normal distribution measurement data was expressed as mean ± SD. One-way analysis of variance was used for comparison of means among multiple groups, and SNK test was used for pairwise comparison. The measurement data of non-normal distribution is expressed as median M (P25–P75). After the natural logarithm is converted to the normal distribution data for analysis, the nonparametric statistical method is used for comparison between groups. Nonparametric test was used to compare data between groups. Correlation analysis used Pearson correlation analysis. Covariance analysis was used to compare the differences in BPV between groups, and multiple stepwise regression analysis was performed on target organ factors related to BPV. *P* < .05 is statistically significant.

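### The aim concerns salt, BPV and organ damage jointly, but no stated analysis is specified with all three, so neither the BPV–damage link given salt nor the salt–damage link given BPV is secured

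*Protocol article*

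**What the plan says.** Section 2.1 of the protocol article gives the aim as a relation among three quantities: "The objective of this study is to investigate the relationship among high salt intake, BPV, and TOD in patients with hypertension". The Introduction names the same gap, saying that "the relationship among high salt load, BPV, and TOD in patients with hypertension is unclear". The abstract's wording is slightly different: "To clarify the relationship between high salt load and BPV and TOD in patients with hypertension".

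The design is stated plainly ("This study is a cross-sectional study") and the size is 600 patients. Sodium is used to form groups in section 2.5.6: "Based on the quartiles of the 24-hour urine sodium, the enrolled population was divided into low sodium group", followed by three higher groups. Section 2.5.3 adds a second grouping, splitting the coefficient of variation of systolic pressure at 12%.

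Section 2.7 lists the analyses: one-way ANOVA with SNK pairwise comparisons, nonparametric group tests, and Pearson correlation. For the multivariable methods it says "Covariance analysis was used to compare the differences in BPV between groups", and it then gives a stepwise multiple regression concerning target-organ variables related to BPV. The significance level is 0.05.

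**The concern.** A question about three quantities needs at least one analysis that contains all three. Section 2.7 gives each of its two multivariable methods a task, and neither task is the three-way question. Covariance analysis is assigned to BPV across groups. Stepwise regression is assigned to organ measures and BPV, and sodium is not mentioned.

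The text therefore does not secure either of the two estimates that the aim calls for: BPV with organ damage at a given sodium level, and sodium with organ damage at a given BPV. If salt is related to both BPV and organ damage, BPV and organ damage will correlate even when BPV contributes nothing. An analysis without sodium would report that correlation as a finding about BPV. Section 2.1 wants to identify risk factors for organ damage, so this error would bear directly on the study's conclusion.

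**Working it through.** **Step 1. What each stated analysis contains (section 2.7).**

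| Analysis | Sodium | BPV | Organ measure | All three specified? |
|---|---|---|---|---|
| One-way ANOVA/SNK, nonparametric tests | as the grouping, or not at all | one outcome at a time | one outcome at a time | no |
| Pearson correlation | two variables at a time | | | no; no partial correlation named |
| Covariance analysis | probably the grouping (which groups is not said) | outcome | not mentioned | no; covariates not named |
| Stepwise regression | not mentioned | yes | yes | no; outcome unclear, candidates not named |

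**Step 2. Inputs for the size of the problem.** From the documents: n = 600 (abstract) and a significance level of 0.05 (section 2.7; two-sided is assumed). The documents give no correlations, so these are assumed: salt–BPV r = 0.3, 0.4 or 0.5; salt–damage r = 0.3; BPV with no effect on organ damage. The protocol gives no basis for 600, so there is no figure of its own to reproduce.

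**Step 3. Induced correlation.** If salt alone connects the two, r(BPV, damage) = r(salt, BPV) × r(salt, damage):
- 0.3 × 0.3 = 0.09
- 0.4 × 0.3 = 0.12
- 0.5 × 0.3 = 0.15

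**Step 4. Chance that the unadjusted test is significant.** By Fisher's z, this is about Φ(atanh(r) × √(n − 3) − 1.96), with √597 = 24.43:
- r = 0.09: 0.0902 × 24.43 = 2.205; Φ(0.245) ≈ 60%
- r = 0.12: 0.1206 × 24.43 = 2.946; Φ(0.986) ≈ 84%
- r = 0.15: 0.1511 × 24.43 = 3.693; Φ(1.733) ≈ 96%

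**Step 5. The same test with sodium in the model.** The numerator of the partial correlation is r(BPV, damage) − r(salt, BPV) × r(salt, damage), which is 0 in every row. The test then rejects at its nominal rate, about 5%.

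**Step 6. Check by simulation** (n = 600, 2,000 runs per setting, both salt paths equal, BPV inert):

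| Salt paths | BPV–damage significant, unadjusted | BPV–damage significant, adjusted for sodium |
|---|---|---|
| 0.3 | 59.8% | 4.9% |
| 0.4 | 97.2% | 5.2% |
| 0.5 | 100% | 4.0% |

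The first row matches step 4. The other two use a larger salt–damage path than step 4, so the induced r is 0.16 and 0.25.

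**Step 7. Do the pairwise results tell the structures apart?** With paths of 0.4, all three Pearson tests were significant in 97 to 100% of runs under each of three structures: salt related to damage only through BPV, salt behind both with BPV inert, and all three links present. The pattern of pairwise significance therefore does not distinguish them. With sodium and BPV in one model, the first structure showed sodium significant in about 5% of runs and BPV in 100%. The second showed the reverse, and the third showed both in 100%.

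**The case against.** Four points can be made for the plan.

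*The plan is not purely pairwise.* A reader might infer that every named analysis handles only two quantities. The document does not support that. Covariance analysis and multiple stepwise regression are multivariable, and nothing in section 2.7 excludes sodium from either. In the simulation with paths of 0.3 to 0.5, a stepwise model of organ damage offered both sodium and BPV kept the right variables in about 95 to 100% of runs. This point stands. The defect is that no analysis is specified with all three, not that none could hold them.

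*Variable lists may sit in a fuller document.* This is a condensed article, and covariate and candidate lists are commonly left elsewhere; their absence alone is no fault. What remains is what the article does state: the task given to each multivariable method is not the three-way aim, and the chosen method is stepwise selection. Even with sodium as a candidate, selection may remove sodium or BPV and leave no adjusted estimate for the one removed.

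*Mediation is not the aim.* A reader might infer that the plan should establish whether salt acts through BPV. The documents speak of a relationship or correlation and never set that question. With a cross-sectional design, no regression would settle direction. This stands in full.

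*Pairwise tests do not necessarily miss a salt pathway.* If salt relates to damage only through BPV, with both links at an assumed 0.20, the salt–damage r is 0.20 × 0.20 = 0.04 and its test is significant in about 16% of studies. It is tempting to call that a loss caused by the plan. Yet each link has Fisher-z power of about 99.86% (atanh(0.20) × 24.43 = 4.953; Φ(2.993)), so two ordinary Pearson tests would show both in about 99.7% of studies (0.9986²). The joint model gains no power there, and with links of 0.40 the salt–damage test itself is significant in about 97%. This argument against the plan is dropped.

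**Conclusion.** The point holds in a limited form. The aim is three-way, and no stated analysis secures the BPV–damage association adjusted for sodium or the sodium–damage association adjusted for BPV. If sodium is left out of the regression, which the text permits but does not state, a BPV–damage link produced by salt would be declared significant in about 60 to 96% of studies of 600, instead of about 5%.

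That range rests on assumed correlations (salt–BPV 0.3 to 0.5, salt–damage 0.3, BPV inert), linear relations and a two-sided 0.05 test. Weaker correlations would give a smaller excess. The mismatch between aim and stated analyses does not depend on these values. It should be corrected because correction is nearly free, but it does not make the study unable to answer its question.

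**What to change.** In section 2.7, replace the stepwise selection with a prespecified regression for each organ measure as outcome (carotid IMT, LVMI, the renal measures):

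1. Force in 24-hour urinary sodium as a continuous variable and the chosen BPV index together, with a listed set of confounders that section 2.5.1 already collects, such as age, sex, BMI and antihypertensive medication.
2. Report both mutually adjusted coefficients with 95% confidence intervals, whether or not they are significant.
3. Add 24-hour mean blood pressure as a separate further step. Entering it together with BPV would mix the two, because the Introduction itself says that high salt intake raises blood pressure.
4. State that the results are cross-sectional associations. No mediation claim or product of coefficients is needed.

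The sodium-quartile comparisons can stay as description. The cost is a few lines of text and a little more analysis work, with no new data.

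One limit should be stated. With 600 patients the smallest partial correlation detectable with 80% power is about 0.114 (two-sided 0.05), so a non-significant adjusted coefficient should be read from its interval and not as absence of association.

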### Design and registration

2.2

This trial was registered in the Chinese Clinical trial registry, ChiCTR2000029243. The flow chart of this study is shown in Figure 1. This cross-sectional study will be conducted at the Fifth People's Hospital of Chengdu City, Sichuan Province from April 2020 to March 2022.

**Figure 1 F1:**
[figure not shown]
Flow chart of protocol. Ccr = creatinine clearance rate, IMT = intima–media thickness.

### Participants and eligibility

2.3

#### Inclusion criteria

2.3.1

##### Participation of the population with primary hypertension

2.3.1.1

Outpatients and inpatients with primary hypertension are over 18 and are not limited in gender. The diagnostic criteria for hypertension are based on 2010 Chinese guidelines for the management of hypertension.

##### Exclusion criteria

2.3.1.2

Participants who will meet any of the following will be excluded:

(1)Acute or chronic renal insufficiency: eGFR ≤45 mL/minute(2)Severe cardiovascular disease(3)Exclude patients with malignant tumors, hematological diseases, rheumatic immune system diseases(4)Heart failure (systolic)(5)Take routine dose or overdose of diuretics continuously for 2 weeks (but the fixed compound of RASI + 12.5 mg thiazide diuretics can be included).

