#### Questionnaire

2.5.1

The participants will complete a questionnaire that would include general sociodemographic information (e.g., age and sex), personal habits (e.g., smoking, alcohol consumption, sleep pattern, and dietary habits), anthropometric measurements (e.g., height, weight, and BMI), pregnancy, menstrual pattern and history, history of present illness, medication history, history of hypertension in relatives, and relevant comorbidities (e.g., cerebrovascular disorders, heart failure, coronary disease, chronic renal failure, and aortic disease).

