#### Target organ measurement standard

2.5.5

1.Blood vessels: Detection of carotid IMT: The patient lies on his back and turn the head to the opposite side. The distance between the intimal surface of the common carotid artery bifurcation 1 cm non-plaque and the outside of the median was measured, and the maximum value was taken on both sides. According to the relevant diagnostic criteria in the 2010 Chinese guidelines for the management of hypertension, the carotid intima media thickness >0.9 mm is defined as thickening and the local protrusions protrude from the arterial lumen >0.5 mm or IMT > 1.5 mm is defined as carotid atheromatous plaque.2.Heart: LVMI: Measure the left ventricular end diastolic diameter (LVDd), interventricular septum, and left ventricular posterior wall, measure 3 consecutive cardiac cycles and take the average. According to the Devereux formula, calculate left ventricular mass (LVM) and LVMI: LVM (g) = 0.8 × 10.4 × ([IVST + PWT + LVDd]^3^ − LVDd^3^) + 0.6; LVMI = LVM / body surface area.3.Kidney: Serum creatinine or endogenous Ccr: 24-hour urine A. MA is defined as negative urine routinely detected protein, and urinary albumin excretion rate is 30 to 300 mg/24 hour.

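### Patients with diabetes may enrol and their albuminuria and carotid thickening count as organ damage, but the tests named for sodium against organ damage cannot adjust for diabetes

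*Protocol article*

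**What the plan says.** **Who enters.** Section 2.3.1.1 is broad: "Outpatients and inpatients with primary hypertension are over 18 and are not limited in gender". Section 2.3.1.2 lists five exclusions. The one on other diseases is "Exclude patients with malignant tumors, hematological diseases, rheumatic immune system diseases", and the renal one is "Acute or chronic renal insufficiency: eGFR ≤45 mL/minute". Diabetes is in neither.

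**What is recorded.** The questionnaire (2.5.1) covers "relevant comorbidities (e.g., cerebrovascular disorders, heart failure, coronary disease, chronic renal failure, and aortic disease". The list is introduced as examples, and diabetes is not one of them. Medication history and history of present illness are also collected. The schedule of data collection (Table 1) is not visible in the text supplied.

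**What counts as damage.** In section 2.5.5, microalbuminuria requires a negative routine urine protein and that "urinary albumin excretion rate is 30 to 300 mg/24 hour". For the vessels, "the carotid intima media thickness >0.9 mm is defined as thickening". Both are thresholds with no reference to cause.

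**How it is compared.** Section 2.5.6 groups by sodium only: "Based on the quartiles of the 24-hour urine sodium, the enrolled population was divided into low sodium group", and so on up to a high sodium group. Section 2.7 names one-way ANOVA with SNK, nonparametric tests and Pearson correlation as general methods. It assigns covariance analysis to differences in BPV between groups, and stepwise regression to organ factors related to BPV. It names no covariates for either.

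**The concern.** The study asks how salt intake and BPV relate to organ damage in hypertension. Diabetes is a recognised cause of both albuminuria in the scored range and carotid thickening, so the kidney and vessel measures partly reflect a second disease. The eGFR cut-off does not solve this, because a diabetic patient with albuminuria and an eGFR above 45 mL/minute stays eligible.

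The consequence depends on one further condition. If diabetes is more common in some sodium quartiles or BPV groups than in others, it produces an association between salt or BPV and TOD that neither exposure caused. If it is evenly spread, it only adds variation to the outcomes and weakens the comparisons.

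This is more than a covariate list left for later. For sodium against TOD, the methods named have no place to put a covariate, so naming diabetes in an analysis plan would not help unless the method also changed. For BPV against TOD there is a regression, but stepwise selection decides what stays in it.

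**Working it through.** The plan gives no figure to reproduce: 600 patients are stated without power, effect size or SD, and no rate of diabetes or albuminuria is given. The check is a reading of the methods followed by an illustration.

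**1. Which planned analysis could adjust for diabetes**

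| Comparison | Method named in 2.7 | Can it adjust? |
|---|---|---|
| Sodium group vs TOD | ANOVA/SNK, nonparametric tests, Pearson | No |
| Group differences in BPV | Covariance analysis, covariates unnamed | Yes, if diabetes is chosen |
| BPV vs TOD | Stepwise regression, candidates unnamed; Pearson | Regression only if diabetes is offered and retained; Pearson no |

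**2. Share of microalbuminuria linked to diabetes**

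Assumed: diabetes share p = 0.15 to 0.30; microalbuminuria in 35% with diabetes and 15% without. From the protocol: N = 600.

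- All cases, as a proportion: T = 0.35p + 0.15(1 − p)
- Cases in diabetic patients: 0.35p / T
- Excess linked to diabetes: (0.35 − 0.15)p / T

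| p | T | Cases of 600 | In diabetic patients | Excess linked to diabetes |
|---|---|---|---|---|
| 0.15 | 0.0525 + 0.1275 = 0.18 | 108 | 0.0525/0.18 = 29% | 0.03/0.18 = 17% (18 cases) |
| 0.30 | 0.105 + 0.105 = 0.21 | 126 | 0.105/0.21 = 50% | 0.06/0.21 = 29% (36 cases) |

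The last column is the relevant one. Under these inputs, 15% of the diabetic patients would have had albuminuria anyway.

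**3. False sodium–microalbuminuria association, lowest vs highest quartile**

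600/4 = 150 per group, with no true sodium effect. The rate in a quartile with diabetes share d is d × m1 + (1 − d) × 0.15, where m1 is the rate in diabetic patients (assumed 25% or 35%). Rejection uses a two-sided normal approximation at 0.05; the protocol does not state sidedness.

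| Diabetes, lowest vs highest | m1 | Rates | Odds ratio | Rejection |
|---|---|---|---|---|
| 20% vs 20% | 25% or 35% | equal | 1.0 | 0.05 |
| 15% vs 25% | 25% | 0.165 vs 0.175 | 1.07 | 0.06 |
| 15% vs 25% | 35% | 0.18 vs 0.20 | 1.14 | 0.07 |
| 10% vs 30% | 25% | 0.16 vs 0.18 | 1.15 | 0.07 |
| 10% vs 30% | 35% | 0.17 vs 0.21 | 1.30 | 0.14 |

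Last row: SE = √(0.17 × 0.83/150 + 0.21 × 0.79/150) = 0.0452; z = 0.04/0.0452 = 0.88; rejection = Φ(0.88 − 1.96) + Φ(−0.88 − 1.96) ≈ 0.14.

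**4. False Pearson correlation, N = 600**

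Assumed: diabetes in 10–30%, shifting sodium or BPV by a = 0 to 0.4 SD and the TOD measure by b = 0.3 to 0.5 SD. With v = p(1 − p),

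r = v·a·b / √[(1 + v·a²)(1 + v·b²)].

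- a = 0: r = 0, type I error 0.05.
- p = 0.20, a = 0.2, b = 0.3: r = 0.010, type I error 0.06.
- p = 0.30, a = 0.4, b = 0.5: v = 0.21; r = 0.042/√(1.0336 × 1.0525) = 0.040; z = atanh(0.040) × √597 = 0.98; type I error 0.17.

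Across these ranges r is 0 to 0.04 and type I error 0.05 to about 0.17.

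**The case against.** The best defence has four parts.

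**Diabetes may be recorded.** The comorbidity list is open, medication history would reveal treated diabetes, and Table 1 is not visible. This stands. A reader might infer that the study ignores diabetes altogether, but the documents do not show that. They show only that the readable text does not name it and that no stated analysis uses it.

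**Covariates belong in the analysis plan.** This stands for the covariance analysis and partly for the regression. It does not stand for sodium against TOD, where the methods named take no covariate, nor does it remove the risk that stepwise selection drops diabetes.

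**Admitting diabetic patients is legitimate.** Agreed. The aim concerns patients with hypertension, and many have other diseases. A reader might infer that the exclusion list is wrong; nothing in the documents requires that. The protocol also never says that each case over a threshold was caused by hypertension. The difficulty lies in the analysis.

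**The same could be said of age, BMI or antihypertensive drugs.** True, and changing the method for sodium against TOD would help with those too. Diabetes is singled out because it directly causes two of the scored outcomes and, unlike age and BMI, is not named for collection in the readable text.

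**Conclusion.** The gap is real and cheap to close. Diabetic patients are eligible, kidney and vessel damage are scored by threshold alone, the stated sodium–TOD tests cannot adjust for diabetes, and the BPV–TOD regression may discard it.

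Its size cannot be fixed from the documents. Under the assumed rates, 17–29% of microalbuminuria cases are excess linked to diabetes. Under the assumed imbalances and shifts, type I error lies between 0.05 (no imbalance) and about 0.17. That is a small to moderate bias.

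Three stronger readings are not supported:

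- **That a false association will occur.** This needs diabetes to differ by sodium quartile or BPV group, and no section says that it does. Without that difference, the effect is noise.
- **That 29–50% of microalbuminuria is diabetic damage.** That range counts every case in a diabetic patient, including those expected without diabetes.
- **That the false-positive rate is about 20%.** A split into halves of 300 with a spurious difference of 0.09 SD (0.6 SD × 15 points) gives z = 0.09/√(2/300) = 1.10 and a rate of 0.20. No such contrast is planned: section 2.5.6 uses sodium quartiles and section 2.5.3 splits CV-SBP at 12%, not at the median.

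**What to change.** 1. In section 2.5.1, name diabetes status as a recorded item, from history, medication, or glucose measured in the blood sample already drawn.
2. In section 2.7, analyse sodium against TOD, and BPV against TOD, by regression or covariance models for albumin excretion, creatinine clearance and IMT. Force diabetes in rather than leaving it to stepwise selection. The unadjusted tests can stay as description.
3. Pre-state a sensitivity analysis that repeats these models without diabetic patients.

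Eligibility does not need to change. The cost is one data item (or one assay on existing blood), one model term, and a smaller set in the sensitivity analysis: at the assumed 15–30% diabetes, 420 to 510 of the 600 patients would remain (600 × 0.70 and 600 × 0.85).
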